### Participant timeline {13}

[The participant timeline is reflected in the SPIRIT diagram included as Fig. 1 in this submission]

### Sample size {14}

#### Statistical power and sample size

An a priori power analysis has been conducted using G*Power V.3.1 for an ANCOVA model estimating fixed effects, main effects and interactions [44]. A medium effect size (*f*=0.25) with power set to 0.80 and alpha set to 0.01 (adjusted given multiple tests and therefore to control for type I error rate inflation) will be sought. Inclusion of six covariates (gender; age; ethnicity; occupation; approximate time spent in places where wearing face coverings would be mandatory; imagery ability) was specified. Power analysis indicated that a minimum sample size of 254 will be required. In developing the recruitment strategy, it is important to be mindful of introducing attrition bias, i.e. bias created by retaining participants with particular characteristics in a way that alters the complexion of the sample. Guidance on acceptable attrition levels has indicated that > 20% study attrition increases the risk of attrition causing serious threats to study validity [45] though debate surrounds precisely when attrition bias may most threaten study validity (e.g. [46, 47]). The study aim is, therefore, to recruit 312 individuals at baseline/T1 to meet a required sample size of 260 at follow-up/T3 (i.e. allowing for no more than 20% attrition).

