#### Behavioural measure

The complete text for the behaviour and psychological measures is included as an online supplementary resource. Self-reported face covering adherence will be measured using a single item based on previously published work [32], adapted to a UK policy/guidelines context. Participants will read the following text: ‘In the past week, when you have gone outside your home for work, grocery shopping, or other activities that involved using public transport, visiting shops/supermarkets, being in enclosed public spaces where social distancing may be difficult, or being in public spaces where you come into contact with people you do not normally meet, how often did you wear a cloth face covering that covered your nose and mouth?’. Participants will provide a response using response items ranging from ‘1’ (never) to ‘5’ (always). This measure of behaviour will be recorded at T1 and T3 only.

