## Statistical methods

### Statistical methods for primary and secondary outcomes {20a}

#### Planned statistical analyses

Across T1–T3, Mean/SD values will be reported for behaviour and the psychological variables and percentages (of total sample) will be reported for demographic variables. Hypotheses stated previously will be tested via a series of ANCOVAs. Intervention condition will be a between-participants variable (outcome, process, combined, control) and time will be a within-participants variable (T1, T2, T3). The primary outcome (face covering behaviour) and secondary outcomes (intention, attitude, subjective norms, PBC, barrier self-efficacy) will be assessed as separate dependent variables. A factorial superiority framework will be adopted for this trial. This approach is preferred to a parallel group trial because it will permit testing for superiority of assignment to a specific imagery exercise technique (e.g. outcome imagery), regardless of study condition, rather than comparing simple assignment to one of the four conditions. Consistent with previous mental imagery interventions, demographic variables will be included as covariates. Where statistically significant effects are demonstrated from ANCOVA analyses, simple effects analyses will be conducted from which estimated marginal means will be reported for all primary and secondary outcome variables. The alpha level will be set at 0.01 for all analyses to control for Type I error rates. Moderation effects of personality traits (conscientiousness, narcissism, Faith in humanity, Kantianism, Humanism) on study intervention effects will be assessed using the PROCESS software macros (V.3.4) on IBM SPSS (V.26).

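### The stated 80% power is for a single-occasion between-participants ANCOVA, not for the planned mixed model with time as a factor; power for the planned test is undocumented

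*Protocol article*

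**What the plan says.** Under *Statistical power and sample size*, the protocol describes a G*Power calculation "for an ANCOVA model estimating fixed effects, main effects and interactions". Its inputs are "A medium effect size (*f*=0.25"), with "power set to 0.80 and alpha set to 0.01". The covariate list opens "Inclusion of six covariates (gender; age; ethnicity; occupation" and goes on to time spent where face coverings are mandatory and imagery ability. Behaviour at baseline is not in the list. The result is stated as "Power analysis indicated that a minimum sample size of 254 will be required". No number of measurement occasions and no correlation between occasions enters the calculation.

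Under *Planned statistical analyses*, the model has four-level condition as the between-participants variable, and "time will be a within-participants variable (T1, T2, T3"). The *Design* section gives the same structure as a 2 × 2 × 3 layout. The analysis section also adopts a factorial framework, so that each imagery technique can be tested regardless of arm. On the significance level it agrees with the sample-size section: "The alpha level will be set at 0.01 for all analyses to control for Type I error rates".

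Under *Outcomes*, the primary outcome is self-reported behaviour at T3. On when it is collected, *Behavioural measure* says: "This measure of behaviour will be recorded at T1 and T3 only". Footnote 2 of Table 1 says the same.

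**The concern.** The sample-size section and the analysis section describe different tests. In the powered test, each person contributes one score and the four arms are compared on it. In the planned model, T1 is a level of the outcome and not a covariate. That model offers two kinds of intervention test:

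- **Condition by time.** This asks whether change from T1 differs between arms. Its power depends on the T1–T3 correlation.
- **Condition main effect.** This averages over occasions, including T1, where randomised arms do not differ in expectation. The effect is diluted.

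Neither is the test behind 254. A three-level time factor also cannot apply to an outcome collected on two occasions. What is at stake is how the primary result will be read: a null finding would be set against a claimed 80% power that was never worked out for the test used.

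**Working it through.** **Inputs from the protocol.** f=0.25; alpha 0.01; power 0.80; six covariates; minimum N=254 (all from *Statistical power and sample size*); four arms allocated 1:1:1:1 (*Sequence generation*); behaviour at T1 and T3 only (*Behavioural measure*).

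**Assumptions, not in the protocol.** f=0.25 describes the spread of arm means at T3; no T1 difference; equal variance at T1 and T3; T1–T3 correlation ρ, shown over a range. The 1-df figures assume that f=0.25 applies to that single contrast.

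**Step 1: reproduce 254.** Use the noncentral F with λ = f²N and df2 = N − 4 − covariates. At N=254, λ = 0.0625 × 254 = 15.875 and df2 = 254 − 4 − 6 = 244. With 3 numerator df, power is 0.802, and at N=253 it is just below 0.80. So 254 is exactly the 3-df, four-arm, one-score figure. Other numerator df give a different minimum: 191 (1 df), 227 (2 df) and 311 (6 df).

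**Step 2: effect size for each candidate test of behaviour.** Let σ be the SD at one occasion.

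- Condition by time with two occasions is an analysis of change scores. The change has variance 2σ²(1−ρ), so f = 0.25/√(2(1−ρ)).
- The condition main effect is an analysis of the T1/T3 average. The spread of means is halved and the variance is σ²(1+ρ)/2, so f = 0.125/√((1+ρ)/2).
- In an ANCOVA of T3 on T1, the residual variance is σ²(1−ρ²), so f = 0.25/√(1−ρ²), with seven covariates and df2 = 243.

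**Step 3: two worked points (3 df).** At ρ=0.3 the change-score test has f = 0.25/√1.4 = 0.211, λ = 0.0625/1.4 × 254 = 11.3 and power 0.60. At ρ=0.5 the change score has the same variance as a single score, so f is again 0.25 and power is again 0.80.

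**Step 4: power at N=254, alpha 0.01.**

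| ρ (assumed) | Condition × time, 3 df | Factor × time, 1 df | Condition main effect, 3 df | T3 ANCOVA with T1 covariate, 3 df |
|---|---|---|---|---|
| 0.2 | 0.52 | 0.71 | 0.32 | 0.82 |
| 0.3 | 0.60 | 0.78 | 0.28 | 0.85 |
| 0.4 | 0.70 | 0.85 | 0.26 | 0.88 |
| 0.5 | 0.80 | 0.92 | 0.23 | 0.925 |
| 0.7 | 0.975 | 0.99 | 0.20 | 0.99 |

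The 3-df condition-by-time test reaches 0.80 at ρ=0.5. The 1-df contrast reaches it at ρ of about a third (0.81 at ρ=0.34).

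**The case against.** A reader might infer that the trial lacks the power it claims. The documents do not support that. They give no T1–T3 correlation, and with ρ at or above 0.5 the 3-df condition-by-time test has 80% power or more.

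Four further arguments run the same way.

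- **The factorial text points to 1-df effects.** This stands: for such a contrast the threshold falls to about a third, so 3-df figures alone would overstate the risk. It does not remove the mismatch, because the 1-df minimum would be 191, not 254.
- **The meaning of f is not fixed.** If f=0.25 were the size of the interaction itself on G*Power's default repeated-measures scale, 254 would give power above 0.99; two occasions at ρ=0 would need 130. That is a different and larger effect than f=0.25 between arms at T3, and the protocol names neither scale. The argument confirms that the power is undefined, not that it is adequate.
- **The three-level wording may be a template for six outcomes.** This is plausible, since the outcome sections say clearly that behaviour has two occasions, and a two-level model can be fitted. The wording still needs correcting, as the abstract and H1 also refer to behaviour at T2.
- **More people were retained than planned.** The *Trial status* section reports 297 with complete T1 and T3 data. At 297 the 3-df test passes 0.80 at ρ of about 0.42, and the 1-df contrast between 0.2 (0.79) and 0.25 (0.82). Engagement and attention exclusions not yet applied would lower that number.

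It is also fair that the protocol never names the condition main effect as its efficacy test. Equally, it names no single primary test.

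**Conclusion.** The mismatch is established: 254 belongs to a 3-df, one-score, between-participants ANCOVA, and the planned analysis is a mixed model whose time factor does not fit the primary outcome as collected. The stated 80% is not the power of that analysis. Whether the real power is lower or higher cannot be settled from the protocol, because it depends on the unstated correlation, the numerator df and what f refers to.

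If f=0.25 holds at T3 and the arms are equal at T1, the condition-by-time test may sit well under 80% or well above it. The main effect is the exception: under those assumptions it is underpowered at every correlation tried. The condition-by-time test is valid in itself; the fault is that its power was not worked out.

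**What to change.** For the primary outcome, specify an ANCOVA of T3 behaviour on condition, or on the two imagery factors if the factorial test is the primary one. Add T1 behaviour to the covariates listed in the sample-size section, taken at baseline, and drop the within-participants time factor for this outcome. This matches the primary outcome as defined and uses data already collected. It also keeps the 254 justification, since 3-df power is at least 0.80 at every correlation under the assumptions above.

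If the mixed model is kept, give behaviour two time levels, name the primary test and its df, say which effect f=0.25 describes, and restate power over a range of T1–T3 correlations. Do not use the condition main effect as the efficacy test.

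The cost is wording in two sections and, for the ANCOVA, one covariate degree of freedom. Enrolment has ended, and no further participants or measurements are needed.

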**Methods:**

The primary objective of this randomized controlled study is to assess the effectiveness of a mental imagery intervention on wearing face coverings, as a defined core COVID-19 preventative behaviour. Participants will consist of UK university students and university employees of any age. Participants will be randomized to complete an ‘outcome imagery’ or a ‘process imagery’ exercise, both exercises (i.e. a combined condition) or neither exercise (i.e. a control condition). A total of 260 individuals will be recruited into the study. Outcomes for all study condition arms will be assessed at baseline (Time 1), immediately post-intervention (Time 2), and at 1-month follow-up (Time 3).

The primary outcome is frequency of wearing face covering, as reported at T2 and T3. Secondary outcomes include intervention effects on face covering attitudes, social norms, perceived behavioural control and barrier self-efficacy at T2 and T3. Putative moderators of intervention effects are conscientiousness, narcissism and ‘light triad’ personality traits.

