## Trial status

Enrolment for this study began on 19 August 2020 and ended on 28 February 2021. The total number of participants recruited includes a sample with complete data at T1/T2 only (*n* = 465) and a sample with complete data at T1 and T3 (*n* = 297). This study protocol is Version 2.0, dated 9 September 2020.

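### The baseline target of 312 does not allow for 20% attrition: it leaves about 249 at follow-up, short of both the 260 and the 254 that the power statement needs

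*Protocol article*

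**What the plan says.** Three passages of the protocol article bear on this.

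- **Sample size {14}.** The power analysis is for an ANCOVA with power 0.80, alpha 0.01 and six covariates: "A medium effect size (*f*=0.25"). Its result is: "Power analysis indicated that a minimum sample size of 254 will be required". The section then cites guidance that attrition above 20% seriously threatens validity, and from this derives its recruitment aim: "to recruit 312 individuals at baseline/T1 to meet a required sample size of 260 at follow-up/T3 (i.e. allowing for no more than 20% attrition").
- **Abstract, Methods.** "A total of 260 individuals will be recruited into the study".
- **Trial status.** Enrolment has ended. The article reports: "The total number of participants recruited includes a sample with complete data at T1/T2 only". It puts that sample at 465, and counts 297 people whose T1 and T3 data are both complete.

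**The concern.** The baseline target, the attrition allowance and the follow-up requirement are stated together in one sentence, and they do not agree. Adding 20% to the number wanted at the end is not the same as allowing for 20% loss from the number at the start.

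The 20% figure carries weight in the argument. The section treats it as the level beyond which validity is at risk, and sets the recruitment target from it. A reader would conclude that power is protected up to that level, and it is not.

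The plan has little else to fall back on. The retention section {18b} says that no retention measures will be used. The eligibility and data quality sections remove further participants for failed attention checks or poor engagement with the imagery exercise, and the calculation states no allowance for them.

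The abstract raises a separate problem. It presents the T3 completer target as the number recruited, so a reader of the abstract alone takes away the wrong enrolment target.

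**Working it through.** **Inputs.** From Sample size {14}: f = 0.25, alpha 0.01, power 0.80, six covariates, minimum N 254, T3 requirement 260, T1 target 312, attrition up to 20%. From Sequence generation {16a}: four equal groups. The numerator degrees of freedom are not stated.

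**1. Reproducing the 254.** Noncentral F with noncentrality λ = f² × N and denominator df = N − 4 − 6. The smallest N with power of at least 0.80 is:

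| Numerator df | N |
|---|---|
| 1 | 191 |
| 2 | 227 |
| 3 | 254 |
| 6 | 311 |

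Of the values tried, only 3 df (the four-group omnibus test) gives 254. That is taken as the basis of the plan's figure, and it is an inference.

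**2. Reproducing the 312.** 260 × (1 + 0.20) = 312 exactly. The 20% was added to the completer number.

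**3. The inflation that matches the stated allowance.** If a fraction d of those recruited is lost, the T1 target is n / (1 − d):

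- for 260 completers: 260 / 0.80 = 325
- for 254 completers: 254 / 0.80 = 317.5, so 318

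**4. What 312 delivers at 20% loss.** 312 × 0.80 = 249.6, so 249 or 250 completers. That is 10 to 11 below 260 and 4 to 5 below 254.

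**5. The attrition that 312 tolerates.**

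- to keep 260: 1 − 260/312 = 16.7%
- to keep 254: 1 − 254/312 = 18.6%

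**6. Power at the retained N** (f = 0.25, alpha 0.01, 3 df, four groups, six covariates):

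| N at T3 | Power |
|---|---|
| 249 | 0.791 |
| 250 | 0.793 |
| 254 | 0.802 |
| 260 | 0.814 |

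**7. The abstract's figure.** If 260 were the number recruited, 20% loss would leave 260 × 0.80 = 208.

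**8. Reported loss, for context only.** Trial status does not say whether the 297 are part of the 465.

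- If they are, T3 loss is 1 − 297/465 = 36.1%, and 312 recruits at that rate would have left 312 × 297/465 ≈ 199.
- If the two samples are separate, the total is 465 + 297 = 762 and the loss is 1 − 297/762 = 61.0%.

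On either reading the loss was well above 20%. This does not bear on whether the planning arithmetic is right.

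**The case against.** The best defence is the wording. Going from 312 to 260 is a 16.7% loss, which is literally no more than 20%, and the preceding sentence uses 20% as a ceiling rather than a forecast. This does not rescue the figure: a loss of exactly 20% lies inside the stated allowance, and the target fails there.

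The remaining objections concern size, and much of them stands.

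- **The consequence is small.** The shortfall is 13 recruits against 325, or 6 against 318, and about one percentage point of power.
- **The loss below 0.80 applies to the 3-df test.** The design and statistical methods sections describe a 2 × 2 factorial comparison of each imagery technique, and those between-group effects have 1 df. With the other inputs unchanged, power for a 1-df effect is 0.910 at N = 249 and still 0.821 at N = 199. The 3-df basis is nonetheless the one that yields the plan's own 254.
- **The reported loss rate is uncertain and comes after the fact.** It shows that the margin was put under strain, no more.
- **Enrolment is over, and 297 exceeds both 254 and 260.** Trial status does not say whether the 297 are counted before or after the exclusions for inattention and non-engagement. If before, up to 297 − 260 = 37 could be removed before the count falls below 260, and up to 297 − 254 = 43 before it falls below 254.

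None of this makes the sentence as written correct, and no other part of the article corrects it.

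**Conclusion.** The concern holds. A baseline target of 312, a 20% attrition allowance and 260 (or even 254) completers cannot all be true. The target tolerates 16.7% loss to 260 and 18.6% to 254, and at 20% it leaves 249 or 250.

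These figures use only numbers in the article. The power figure of about 0.79 also assumes the 3-df test. The abstract's 260 recruited contradicts the sample size section in its own right.

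This is an error in the planning statement with a modest effect on power. It should be corrected because the sample size justification is wrong as it stands, but it does not undermine the trial.

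**What to change.** Change two sentences.

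1. **Sample size {14}.** State that 312 at T1 allows for 16.7% attrition to 260 at T3 (18.6% to the minimum of 254), and that 20% attrition would have required 325 (318 for 254).
2. **Abstract, Methods.** Give 312 as the number to be recruited at T1 and 260 as the T3 target.

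It would help to add in Trial status whether the 297 are counted before or after the data-quality exclusions. No extra enrolment is needed if at least 260 remain after them.

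The cost is a slightly less favourable stated tolerance. Design, conduct and analysis are unchanged.

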### Recruitment {15}

#### Enrolment

Details of the schedule of enrolment, interventions, and assessments are shown diagrammatically in Fig. 1.

As described above; all measures will be acquired via Qualtrics, an online platform which will host our study questionnaire. A URL link to the Qualtrics hosted survey will be embedded into an email message promoting the study and this promotional message will be sent out in an email circular message to prospective participants (staff and students at UEL and Manchester University). We will follow bi-weekly enrolment drives to maximize the possibility of an even spread of responses throughout the study recruitment phase, and to maintain a consistent promotional presence of the recruitment message. We will aim to complete all study enrolment within six months: recruitment will start in approximately mid-September 2020 and we will aim to complete all study enrolment (i.e. responses at T1, T2 and T3) by late February 2021. Where enrolment continues for longer than 6 months, we will explore ‘date of participant response’ as a covariate in main intervention study analyses. We will supplement our university-focused recruitment approach by also posting a URL link to the Qualtrics-hosted survey twice each week on social media (e.g. on Twitter, via Facebook posts). Participant recruitment will be led by the protocol author (the UEL-based study researcher) and will be supplemented by recruitment activities led by a second researcher based at Manchester University.

## Assignment of interventions: allocation

### Sequence generation {16a}

After participants have completed complete demographic, psychological and behavioural measures at baseline (T1) they will be randomized to the outcome imagery exercise, the process imagery exercise, a combined condition (comprising the outcome and process imagery exercises) or a control condition. The allocation ratio (i.e. the ratio of participant numbers in each of the conditions) is intended to be equal across groups (i.e. 1:1:1:1). Throughout the recruitment period, the protocol author will conduct biweekly checks to audit that roughly equal allocation of participants to conditions has occurred. Randomization will be conducted via a Qualtrics randomizer features embedded in the T1 survey. The Qualtrics randomizer uses a Mersenne Twister pseudorandom number generator approach which is a widely used approach employed within standard statistical packages (e.g. IBM SPSS, Microsoft Excel). This approach follows a random method by which the randomization sequence cannot be determined until participant assignment has occurred while ensuring roughly even distribution of participants across groups. The researcher team will be blind to group assignment at the point of randomization.

### Concealment mechanism {16b}

Details are provided in the ‘Sequence generation {16a}’ section above.

### Implementation {16c}

Details are provided in the ‘Sequence generation {16a}’ section above.

## Assignment of interventions: Blinding

Details are provided in the ‘Sequence generation {16a}’ section above.

### Who will be blinded {17a}

Details are provided in the ‘Sequence generation {16a}’ section above.

### Procedure for unblinding if needed {17b}

Not applicable as unblinding is not anticipated as a required process within this trial.

## Data collection and management

### Plans for assessment and collection of outcomes {18a}

#### Data collection and management

Participant names will not be included in the dataset and each participant will be assigned a study ID. All data will be downloaded in secure form to institutional cloud services (i.e. OneDrive). All data will be backed-up securely and all data files will be securely password protected and encrypted. Throughout project activities, data files and printed materials that are no longer required will be destroyed. Email address data will be stored in a separate document in an encrypted folder and will be destroyed once recruitment is completed. Range and consistency checks will be conducted on all questionnaire data promptly by the research team. Because questionnaire data will be collected using a ‘Force Response’ setting on Qualtrics there will be no missing data for this study. To address incomplete participant responses we will conduct an intention-to-treat (ITT) analysis in addition to the complete case analysis. ITT is an assessment of all trial participants in analysis regardless of whether or not they provided incomplete responses or failed to provide follow-up responses and provides a way of producing an unbiased estimate of intervention efficacy of the intervention in respect of study adherence [48].

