### Plans to promote participant retention and complete follow-up {18b}

Not applicable as plans to promote participant retention and complete follow-up will not be included in this trial.

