### Methods in analysis to handle protocol non-adherence and any statistical methods to handle missing data {20c}

Details are provided in the ‘Statistical methods for primary and secondary outcomes {20a}’ section above.

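### A forced-response setting cannot rule out missing T3 outcomes, and the plan states no way for its intention-to-treat analysis to include people who do not return

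*Protocol article*

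**What the plan says.** Section {18a} of the protocol article (Plans for assessment and collection of outcomes) states that the Force Response setting in the survey software means "there will be no missing data for this study". It continues: "To address incomplete participant responses we will conduct an intention-to-treat (ITT) analysis in addition to the complete case analysis". It defines ITT as covering all trial participants "regardless of whether or not they provided incomplete responses or failed to provide follow-up responses" and says that this gives an unbiased estimate of efficacy.

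Section {20c}, headed as the place for non-adherence and missing-data methods, contains one sentence: "Details are provided in the ‘Statistical methods for primary and secondary outcomes {20a}’ section above". Section {20a} names a series of ANCOVAs with condition between participants and time (T1, T2, T3) within participants. It says nothing about missing values.

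Four other places bear on the point:
- Sample size {14} plans 312 at T1 to keep 260 at T3, allows for at most 20% attrition, and notes that "> 20% study attrition increases the risk of attrition causing serious threats to study validity".
- Outcomes {12} and the Behavioural measure section record the primary outcome, face covering behaviour, at T1 and T3 only.
- Eligibility criteria {10} lists full completion of the questionnaire as a criterion.
- Trial status reports: "The total number of participants recruited includes a sample with complete data at T1/T2 only" (465), and a sample complete at T1 and T3 (297).

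**The concern.** A forced response acts within a survey that someone has opened and is filling in. It has no hold on a person who closes the browser or ignores the invitation a month later. For a primary outcome measured at one month, that second kind of missingness is the one that matters, and the sentence denies it.

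The remedy offered does not fill the gap. ITT says who belongs in the analysis and in which arm. It does not say what stands in for a T3 value that was never collected. A participant lost at T3 has no post-randomisation measurement of the primary outcome, because behaviour is not recorded at T2. If the named model is simply run, those people leave the analysis and the ITT label no longer describes the set analysed.

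At stake is the credibility of the primary comparison. A completers-only estimate would carry an ITT label and a claim of unbiasedness, at a level of loss above what the plan allowed for.

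**Working it through.** **1. The plan's own sample size, and whether the issue is power.** Inputs from Sample size {14}: f = 0.25, alpha = 0.01, power 0.80, six covariates. Numerator df = 3 and four groups are not stated and are inferred here.
- N = 254: noncentrality f²N = 0.0625 × 254 = 15.9; denominator df = 254 − 4 − 6 = 244; power = 0.802. The stated 254 is reproduced.
- N = 297: noncentrality 0.0625 × 297 = 18.6; denominator df = 287; power = 0.88.

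The 297 with T3 data exceed the required 254. The problem is possible bias, not power.

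**2. Loss at T3.** Inputs from Trial status: 465 and 297.
- If the 297 are a subset of the 465: 465 − 297 = 168; 168/465 = 36.1%.
- If the samples are separate, as the word *only* in Trial status might suggest: 465 + 297 = 762; 465/762 = 61.0%.

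Both exceed the planned maximum of 20%. The number randomised is not given. Anyone who left between randomisation and the end of T2 is uncounted, so true loss may be higher.

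**3. Who enters each analysis of T3 behaviour.**
- ITT as defined in {18a}: everyone randomised, including those without follow-up.
- Complete case: those with T1 and T3 behaviour, 297.
- The only model named in {20a}: a conventional ANCOVA with time within participants needs every time point of the outcome, so it too uses 297.
- Eligibility {10}, read literally: someone who does not complete the questionnaire at each time point is not eligible at all. This conflicts with an ITT set that includes non-responders.

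Without imputation or a likelihood-based model, the first set cannot be analysed as defined, and the analysis falls back on the second.

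**4. What the loss can do to the estimate.** Let m be the proportion lost, assumed equal across arms, and let D be the arm difference in returners minus that in non-returners. The difference in all randomised is (1 − m) × (returners) + m × (non-returners). The completer estimate is therefore off by m × D:
- planned ceiling, m = 0.20: 0.20 × D;
- subset reading, m = 0.361: 0.36 × D.

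D is unknown. With no assumption about the missing values, the bounds on an arm difference on the 1–5 item are 2 × 0.361 × 4 = 2.9 points wide. That is an extreme bound, not an expected bias. It shows that the result for all randomised depends on a missing-data assumption that the article does not state.

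**The case against.** The best defence is context. The sentence is tied to the Force Response setting, so it can be read as being about skipped items. The text that follows it deals with people who gave no follow-up, and the sample size allows for attrition. That much stands: the authors did foresee non-return, and a reader should not infer that they overlooked it. But the sentence as written covers the whole study, and on that scope it is wrong.

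The second defence is that an article may leave the imputation or mixed model to a statistical analysis plan, which is not at hand. This also carries weight. A reader might infer that ITT is bound to equal complete case here; the article does not establish that, because an unshown plan could supply a method. What remains is not mere absence of detail. The article makes a false statement, claims unbiasedness for an analysis it gives no means of running, and sends the reader from its missing-data heading to a section with no such method.

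A baseline-adjusted complete-case analysis can also be valid if return depends only on arm and the adjusted covariates. True, but that is an assumption to be stated and tested. The T2 cognitions, which may well predict return, are not among the covariates.

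Three further inferences are tempting and unsupported:
- **Longer imagery exercises cause unequal loss by arm.** Everyone among the 465 had finished the exercise by T2, and no loss by arm is reported.
- **ITT is ranked below complete case.** Saying that one analysis is done in addition to another does not rank them.
- **The T1/T2 data of those lost are thrown away.** T2 is an outcome time for the secondary measures, and nothing says that those data go unused there.

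**Conclusion.** The point holds in a bounded form. The no-missing-data statement is wrong for the study as a whole, and the article's own attrition allowance and counts contradict it. Loss at T3 is 36% if the 297 are a subset of the 465 and 61% if they are not, against a planned maximum of 20%. On the only model the article names, an ITT analysis of T3 behaviour would use the same 297 people as the complete-case analysis. That conclusion is conditional on no imputation or likelihood-based method being specified elsewhere. The completion criterion in Eligibility {10} conflicts with the ITT definition in either case.

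A reader might go on to conclude that the result is biased by some definite amount. The article does not support that. It gives neither outcomes for those lost nor attrition by arm, and it notes that the level at which attrition becomes harmful is debated. What can be said is that the claim of an unbiased estimate has no stated basis.

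**What to change.** 1. In {18a}, confine the sentence to item-level missingness within completed surveys, and say plainly that non-return at T3 is expected.
2. Make the main analysis one of all randomised participants as allocated, and write the method into {20c} in place of the cross-reference.
3. For T3 behaviour, state a method. Multiple imputation by arm from T1 behaviour, T1 and T2 cognitions (intention, attitudes, norms, perceived control, self-efficacy) and covariates is a sound choice, because it uses T2 information that the ANCOVA ignores. Other stated methods could serve.
4. For the psychological outcomes, use a likelihood-based mixed model over T2 and T3 adjusted for T1, so that people with T2 but no T3 still contribute.
5. Keep complete case as a sensitivity analysis and add a delta-adjusted one, for example with non-returners 0.25 and 0.5 points lower. Let the shift differ by arm, since with equal loss a common shift leaves the contrast unchanged.
6. Report the number randomised and attrition by arm at T2 and T3, and say whether the 297 are part of the 465.
7. Reconcile the completion criterion in Eligibility {10} with the ITT set.

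The cost is some rewording and a few more analyses on data already held. No new data collection is needed.
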